### Intervention

The project started at each hospital with a grand round that outlined the project protocol. One physician or nurse with at least two years of experience of clinical pathways was assigned to each hospital in the experimental group, in order to facilitate project implementation (this included staff education in the use of the clinical pathway). The teams included internal medicine physicians, neurologists, physiatrists, epidemiologists, physiotherapists, occupational therapists, nurses, hospital pharmacists, psychologists, social workers and support staff. The teams were formed on a voluntary basis, they received three days training in the development of clinical pathways and then they developed their clinical pathway over a 6-month period. All groups analyzed their care processes, reviewed best evidence (this was provided by senior investigators), defined the appropriate goals of the pathways, compiling the results into protocols and documentation. This included the sequencing of events and expected progress of the patients over time [9,20].

The clinical pathways were analyzed by the EBM unit of the Regional Healthcare Agency of Marche and they were judged consistent with current recommendations for the diagnosis and the treatment of stroke. After the validation of the pathways each unit team educated its staff in the use of the clinical pathway and monitored the use of the pathway. This meant that the clinical pathways used in the study were not completely identical because of organizational adaptations at some sites. However, they all substantially adhered to the existing Italian guidelines on the hospital treatment for stroke [21].

### Data analysis

Data was prospectively collected by local staff for both the interventions and the control groups (physicians and nurses had been trained prior to commencement of the study at two educational events in order to do this). Incentives for the local staff were not used. Data was collected using a standardized data extraction instrument which utilized web technology. This allowed only data without unique personal identifiers, but with a unique study identification code (and therefore anonymous), to be entered into a secure database housed at the University of Eastern Piedmont.

The analysis will be performed by the research team. In addition to common descriptive statistics (Fisher exact and Kruskal Wallis test for categorical and continuous variables, respectively), that will be performed at the cluster level, the differences in the rate of 30-days mortality across groups and according to each variable under study will be evaluated using random-effects logistic regression, thus accounting for the clustering effect [5,22,23]. Variables will be included if significant at the 0.10 level (backward approach), with the exception of age which will be forced to entry. The presence of multicollinearity, interaction and higher power terms will be assessed to check final model validity.

Statistical significance will be defined as a two-sided p-value < 0.05. All analyses will be intention-to-treat and will be carried out using Statistica statistical software.

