### Study evaluations

The primary outcome measure was patient mortality 30-days following the stroke. Thirty-day mortality was defined as the proportion of ischemic stroke events that are fatal within 30 days from the onset. Stroke fatality was chosen as main outcome because it is clinically relevant, objectively measured, and reliably coded [5]. The impact of the clinical pathways, comparing the length of the in-hospital stay, the hospital re-admissions rates, the institutionalization rates after hospital discharge, the patients' dependency levels, and complication rates along all the continuum of the care were also analyzed. The list of outcome indicators is reported in table 1.

**Table 1 T1:** The outcome indicators set

**Indicator**	**Measure**	**Criterion met/expected change**	**Source, Year**
In-hospital death rate within 30 days from admission to hospital	(%)	Differences in rates	Clinical Outcome Working Group, 1995, 1997; NHS Centre for Coding and Classification, 1990
In-hospital death rate within 30 days from stroke attack	(%)	Differences in rates	
Post-discharge death rates (1, 3, 6, 12 months after discharge)	(%)	Differences in rates	
In-patients length of stay	Days	Differences in means	Schmidt WP, 2003
Within 9 days length of stay in hospital patients' rate	(%)	Differences in rates	
Pressure ulcers incidence rate	(%)	0%	Clark M, 1991; Effective Health Care, 1995
Overall in-hospital complications rate	(%)	4%	Adams HP Jr, 2003
Overall post-discharge complications rate	(%)	Differences in rates	
Dependency at discharge	FIM scale	Differences in means	Gompertz P, 1993 Wade DT, 1987
Dependency at 6 months after stroke	FIM scale	Differences in means	Hardwood RH, 1994
Institutionalization at discharge	(%)	Differences in rates	Nikolaus T, 2000 Kalra L, 1995
In-hospital re-admission rate (within 30 days from discharge)	(%)	Differences in rates	Ebrahim S, 1987 Milne R, 1990
Return to pre-stroke functioning in daily life rate (with ADL/case mix adjustment)	(%)	Differences in rates	Early Supported Discharge Trialists (Cochrane 2005, Issue 2)

The quality of the care provided to the patients was assessed by monitoring the use of diagnostic and therapeutic procedures during hospital stay and rehabilitation, and by the use of key quality indicators at discharge as reported in previous studies (table 2). The implementation of organized care was also evaluated (table 3).

**Table 2 T2:** The process indicators set

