### Study sample

A calculation was made to identify the sample size needed to detect a statistical difference in the 30-days mortality rate. As between 8% to 17% of ischemic stroke patients die within 30 days of the incident, it was expected that the clinical pathways would succeed in limiting mortality to 8% and would therefore be clinically relevant [3,15,16]. Based on this goal a sample size of 476 patients (238 in each group) was required for the study to have 80% power at the 5% significance level. The sample size calculation was performed according to standard criteria for cluster randomized trials. The sample size was adjusted using an inflation factor of 1.43 to account for the cluster randomization: 7 clusters per trial arm, cluster size of 24 patients, ICC of 0.018 [17-19].

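### Only 30-day mortality is given a clustered model; Fisher exact at the cluster level does not fit the binary patient indicators in Tables 1 to 3

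*Protocol article*

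**What the plan says.** The Data analysis section of the protocol article names two kinds of analysis.

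- **30-day mortality:** "the differences in the rate of 30-days mortality across groups and according to each variable under study will be evaluated using random-effects logistic regression". The section gives clustering as the reason for this choice.
- **Other variables:** "common descriptive statistics (Fisher exact and Kruskal Wallis test for categorical and continuous variables, respectively), that will be performed at the cluster level".

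The Study evaluations section lists further comparisons between arms: "comparing the length of the in-hospital stay, the hospital re-admissions rates, the institutionalization rates after hospital discharge, the patients' dependency levels, and complication rates". Table 1 gives differences in rates as the expected change for most outcomes, and differences in means for length of stay and the FIM scores. Tables 2 and 3 add process and organized-care indicators, nearly all measured as percentages.

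The Study sample section plans for clustering with "7 clusters per trial arm, cluster size of 24 patients, ICC of 0.018" and states that "The sample size was adjusted using an inflation factor of 1.43 to account for the cluster randomization". The two-sided 0.05 threshold in the Data analysis section is not restricted to mortality.

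**The concern.** The random-effects model has a single dependent variable, mortality. The reference to each variable under study describes covariates of that model, as the next sentence on backward selection with age forced in shows. A logistic model could not serve length of stay or FIM scores in any case. That leaves Fisher exact and Kruskal-Wallis as the only named tests for everything else.

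Fisher exact compares counts in categories. Re-admission, institutionalization, complications, early brain imaging and early aspirin are yes/no for a patient but a proportion for a unit. The stated test and the stated level therefore do not go together for these indicators. An analyst who has to produce a p-value could easily fall back on a pooled patient-level 2×2 table, which drops the clustering that the sample size was inflated to cover.

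The second objective (appropriateness of care) and the third (organized care) rest on these indicators, and the first extends to patient outcomes beyond mortality. The Discussion also singles out organized care, with mortality, as a measure for testing the new hypothesis.

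**Working it through.** **Inputs from the protocol article**

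- Units per arm: 7 (14 in all).
- ICC: 0.018.
- Patients per unit: 24 as stated, or 238/7 = 34 as implied by the target of 238 per arm. Both are carried through.
- Significance level: two-sided 0.05.

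**The plan's own inflation factor**

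- The usual design effect is 1 + (m − 1) × ICC = 1 + 23 × 0.018 = 1.414.
- Using m in place of m − 1 gives 1 + 24 × 0.018 = 1.432, which rounds to the stated 1.43.
- At 34 per unit the usual formula gives 1 + 33 × 0.018 = 1.594.

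**Fisher exact on pooled patients: normal approximation**

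A test that ignores clustering has true two-sided type I error of about 2 × [1 − Φ(1.96/√DE)], where DE is the design effect.

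- 24 per unit: 1.96/√1.414 = 1.648, giving 0.099.
- 34 per unit: 1.96/√1.594 = 1.552, giving 0.121.

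**Simulation under no effect**

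There were 4,000 runs with 7 against 7 units. Binary outcomes were beta-binomial with an assumed event rate of 30%. Continuous outcomes had a normal random unit effect.

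| ICC | Patients per unit | Fisher, pooled patients | Kruskal-Wallis, pooled patients | Kruskal-Wallis, 14 unit rates |
|---|---|---|---|---|
| 0.018 | 24 | 0.083 | 0.097 | 0.048 |
| 0.018 | 34 | 0.108 | 0.119 | 0.048 |
| 0.05 (assumed) | 24 | 0.167 | 0.174 | 0.048 |
| 0.05 (assumed) | 34 | 0.212 | 0.212 | 0.048 |
| 0.10 (assumed) | 24 | 0.254 | 0.264 | 0.054 |
| 0.10 (assumed) | 34 | 0.332 | 0.335 | 0.051 |

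Fisher exact is conservative, so its simulated error lies a little below the approximation. Across methods the error at the protocol's ICC is about 8% to 12%. The protocol gives no ICC for process indicators. The rows at 0.05 and 0.10 show only what would follow if unit practice made it larger.

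**Kruskal-Wallis on unit summaries**

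The last column stays close to 5% throughout. With 7 against 7 units the smallest attainable asymptotic p-value is 0.0017, so significance is within reach. What the test does not supply is covariate adjustment or an estimate of the difference in rates or means that Table 1 refers to.

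**The case against.** The strongest reply is that the sentence has a sensible reading. A unit rate is a continuous quantity and continuous variables go to Kruskal-Wallis, so every percentage in Tables 1 to 3 becomes 14 unit rates compared by a rank test. Fisher exact is then left for categorical unit attributes such as teaching status. This reading respects clustering, and it need not be weak: in simulation at ICC 0.018, with assumed rates of 50% against 30%, power was about 0.80 at 24 per unit and 0.88 at 34, against 0.83 and 0.90 for a t-test on unit counts. The reply stands for Kruskal-Wallis. It does not settle how the binary indicators are handled, because the text assigns Fisher exact to categorical variables without saying that a patient-level yes/no indicator is to be treated as continuous.

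Two further points limit the finding. The tests are labelled descriptive, and the article does not say outright that they are the comparative analysis of the secondary outcomes. The article may also condense a fuller plan. The point is therefore about a stated test that does not fit its stated level. It does not fault the article for leaving out a secondary-outcome model.

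A reader might infer three stronger claims, and the documents support none of them:

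- **Neither test can be used on unit rates.** This is wrong for Kruskal-Wallis, which keeps its level.
- **The secondary tests are nearly powerless.** This would apply to Fisher exact on dichotomised units, where 6/7 against 2/7 gives only p = 0.103. The plan proposes no dichotomisation.
- **The plan will test at about 12%.** That figure needs pooled patients and 34 per unit, whereas the text says cluster level and states a cluster size of 24.

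**Conclusion.** The point holds in limited form. Fisher exact at the cluster level does not fit the binary patient indicators in Tables 1 to 3, and mortality is the only outcome with a named clustered model. The type I error of about 8% to 12% is conditional on the test being run on pooled patients. It rests on the protocol's ICC of 0.018 being applied to these outcomes, on 24 to 34 patients per unit and, in the simulation, on a 30% event rate. Larger errors depend on larger ICCs that the protocol does not give.

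The primary analysis is unaffected. The change is still worth making, because two of the three objectives depend on these indicators and the significance threshold is not limited to mortality.

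**What to change.** Reword the Data analysis section as follows.

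- Keep Fisher exact only for categorical characteristics of the units.
- For the outcomes in Tables 1 to 3, name a method that respects clustering. One option is a mixed model or GEE with a small-sample correction for 14 units. The other is a t-test or rank test on unit means or rates.
- Prefer unit summaries for indicators expected near 0% or 100%. Several have targets of 0% or of all patients, and a mixed logistic model with 14 units may fail to converge there.
- Report the difference in rates or means with a 95% confidence interval for each outcome.

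No new data are needed. The cost is the change of wording, modest extra programming, and intervals wider than a pooled analysis would show.

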### Objectives

The main objective of the trial is to evaluate the effectiveness of the implementation of clinical pathways for acute stroke care and rehabilitation within a sample of Italian hospitals and rehabilitation long-term care facilities. The hypothesis is that clinical pathways would be more effective than usual care in treating stroke patients and that the clinical pathways would reduce both patient mortality and improve patient outcomes.

The secondary objective is to determine whether clinical pathways increase the appropriateness of the care provided to the patients in hospital and through the continuum of the care and its effects on the outcomes.

The third objective is to determine whether clinical pathways help to implement organized care in acute stroke care and rehabilitation facilities and its effects on the outcomes [5].

A pilot study to define baseline levels of performance in acute stroke care and rehabilitation facilities has been described previously in a separate protocol [10].

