**Indicator**	**Measure**	**Criterion met/expected change**	**Source, Year**
Information, advice and support from the multidisciplinary team given to the patients (and with their consent, to the carers)	(%)	Given to all the patients/relatives/care givers	SIGN 64, 2002
Use of referral protocols (to neurovascular clinics and admission to stroke unit)	(%)	Given to all the patients	NHS QIS (CSBS-PPI 2002) Clinical Standards, 2004; CHD/Stroke Task Force, 2001; SPREAD, 2005
Use of clinical protocols (at least 5 of the following)	(%)	Given to all the patients	CHD/Stroke Task Force, 2001; CSBS 2002; Antiplatelet Trialists' Collaboration, 1994; SIGN 13, 1997; European Atrial Fibrillation Trial, 1993; Hebert PR, 1997; SIGN 14, 1997; Antithrombotic Trialists' Collaboration, 1998
- Stroke treatment/management protocols			
- Antiplatelet/anticoagulant protocol			
- Diabetes treatment protocol			
- Atrial fibrillation therapy protocol			
- Blood pressure lowering protocol			
- Cholesterol lowering protocol			
- Suspected carotid stenosis protocol			
- Smoking cessation protocol			
Use of (local) admission to social services protocols	(%)	Given to all patients	Report to the Dept. of Health, 2000
Use of CT/MRI brain scan within 48 hours from admission	(%)	80%	SIGN 14, 1997; Wardlaw JM, 2003
Aspirin treatment within 48 hours from admission	(%)	Given to all patients	Gubitz G (Cochrane 2003)
Swallow screen test on day of admission	(%)	Given to all patients	SIGN 20, 1997
Blood pressure assessment	(%)	Given to all patients	Progress, 2001; NHS QIS (CSBS 2002); Clinical Standards, 2004
ECG/ECD within 24 hours from admission	(%)	Given to all patients	SIGN 13, 1997
Continuous monitoring within 48 hours from admission (see parameters below)	(%)	Differences in rates	SIGN 13, 1997; New Zealand Guidelines Group, 2003; Canadian Stroke Network and the Heart and Stroke Foundation of Canada, 2006
- Blood pressure			
- Glycaemia			
- Electrolitemia			
- Breath			
Before discharge total assessment (see parameters below)	(%)	Given to all patients	MRC/BHF Heart Protection Study, 2002, 2003; SIGN 24, 1998
- Tobacco smoke			
- Lipemia			
- Glycaemia			
Use of discharge plan (and communication)	(%)	Given to all the patients/relatives/care givers	SIGN 24, 1998
Use of SIGN guidelines-based discharge plan	(%)		SIGN 24, 1998
Use of discharge summary and information (information pack)	(%)		RCPE, Consensus Panel, Nov 2000; SIGN 65, 2003

**Table 3 T3:** The organized care indicators set

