**Indicator**	**Measure**	**Criterion met/expected change**	**Source, Year**
Use of organized care	OCI	Differences in rates	Saposnik G, 2007
Admission to stroke unit	(%)	100%	NHS QIS (CSBS 2002) Clinical Standards, 2004; CHD/Stroke Task Force Report, 2001; SIGN 13, 1997; SIGN 64, 2002
Stay in stroke unit within 24 hours after admission and until the end of in-hospital rehabilitation	(%)	70%	
Use of case managers (physiotherapists, occupational therapists, nurses specialized in stroke care)	(%)	Given to all the patients	RCP IWP/S, 2000; SIGN 64, 2002
Use of stroke team	(%)	Given to all the patients	CHD/Stroke Task Force, 2001; SIGN 64, 2002
Assessment for rehabilitation needs by a member of the stroke team within 48 hours after admission	(%)	Given to all the patients	Brown M, 2000
Patients' needs assessment and planning rate for post-discharge services	(%)	Given to all the patients	RCPE, Consensus Panel, Nov 2000; NHS QIS Clinical Standards, 2004
Follow-up rate within 3 months after discharge (by specialist/stroke team)	(%)	Given to all the patients	

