## Discussion

The aim of this study is to improve the quality of care through clinical pathways and thus should not imply any risk for the patients affected by the study. It is difficult to imagine that interventions based on better evidence and appropriate use of technologies and drugs could worsen the quality of care when compared to usual care. However despite continuing international interest in implementing clinical pathways, the evidence base for their effectiveness in improving the quality of stroke care is still inconclusive [8].

Clinical pathways could be defined as a complex intervention in which a number of separate elements are essential to the functioning of the intervention, but the "active ingredient" that is effective is difficult to specify [11]. For this reason it could be problematic to evaluate properly clinical pathways mainly because of the difficulty of keeping the intervention replicable and recognizable. However we think that a cluster randomized controlled trial design is the most appropriate to evaluate clinical pathways [24]. To standardize the intervention we defined as standard the steps in the change process or the key functions that the elements of the intervention were meant to improve according to each context. Moreover our indicators were driven by the theory and concerned the functions provided by the key elements of the clinical pathways that were based on expected adherence to the same evidences. So we think that this helped to keep the integrity of the intervention in each site [10,25].

We also think that the outcome measures chosen were well-suited to measuring the impact clinical pathways have on stroke care, because they were measures that evaluated most of the perspectives of stroke care from acute to rehabilitation settings. In particular two outcome measures – mortality and organized care – can help to investigate the new hypothesis which is to understand how clinical pathways can work. In fact the management of patients affected by stroke involves the expertise of several professionals, which can result in poor coordination or inefficiencies in patient treatment, and clinical pathways can significantly improve the outcomes of these patients. However, the active ingredient of clinical pathways is unclear, so we think that our study will help to better understand which mechanisms within the clinical pathways can really improve the quality of care.

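### 30-day mortality is modelled on every study variable with no limit to baseline, so care indicators that require survival could look protective with no effect

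*Protocol article*

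**What the plan says.** The Data analysis section of the protocol article gives one modelling rule for the primary outcome: "the differences in the rate of 30-days mortality across groups and according to each variable under study will be evaluated using random-effects logistic regression". It continues: "Variables will be included if significant at the 0.10 level (backward approach), with the exception of age which will be forced to entry". Neither sentence defines the set of variables or confines it to the admission characteristics listed under Study subjects (age, sex, comorbidity index, risk factors, FIM).

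The care indicators matter here because of the Objectives section. Objective 3 is to determine whether "clinical pathways help to implement organized care in acute stroke care and rehabilitation facilities and its effects on the outcomes"; objective 2 asks the same of appropriateness of care. The Discussion adds: "In particular two outcome measures – mortality and organized care – can help to investigate the new hypothesis".

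Death is counted over 30 days from stroke onset (Study evaluations). The indicators in Tables 2 and 3 are recorded at various times after admission. Some have a short window, such as "Assessment for rehabilitation needs by a member of the stroke team within 48 hours after admission". Others concern discharge or what follows it, such as "Patients' needs assessment and planning rate for post-discharge services".

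**The concern.** An item due on day 2, at discharge or at three months can be delivered only to a patient who is alive then. If earlier deaths are recorded as not having had the item, the outcome determines the exposure: deaths accumulate among patients without the item, and it looks protective even when it does nothing.

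Two things are at stake. The analysis meant to show which part of a pathway works could favour the items delivered latest, simply because they are delivered latest. And if these items share a backward-selected model with the arm, they would tend to be retained and could take over part of the arm effect, since a pathway is meant to raise their delivery.

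**Working it through.** The article states no figure on this point, so there is none to reproduce.

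**Which items.** Tables 2 and 3 list 14 + 8 = 22 indicators.
- Seven are tied to discharge or later: pre-discharge assessment, discharge plan, guideline-based discharge plan, discharge summary, stroke-unit stay to the end of rehabilitation, post-discharge needs planning, and 3-month follow-up.
- Five have 24–48 hour windows: brain scan, aspirin, ECG/ECD, continuous monitoring, and rehabilitation assessment.
- The other ten are same-day, organizational or without a stated time.

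**Inputs.**
- 30-day mortality m = (8% + 17%)/2 = 12.5%, the midpoint of the range in Study sample.
- Delivery c among patients alive when the item is due: assumed 70%.
- Share f of 30-day deaths that occur before the item is due: assumed 20%, 35% or 50%.
- The item has no effect on death, and patients who die first count as not given.

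**Closed form.** Given and died: m(1−f)c. Given and survived: (1−m)c. Not given and died: m − m(1−f)c. Not given and survived: (1−m)(1−c). Hence

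OR = (1−f)(1−c) / (1−c+fc).

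m cancels, and the result is below 1 whenever f > 0.

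| f | Mortality if given | Mortality if not given | OR |
|---|---|---|---|
| 20% | 0.0700/0.6825 = 10.3% | 0.0550/0.3175 = 17.3% | 0.24/0.44 = 0.55 |
| 35% | 0.0569/0.6694 = 8.5% | 0.0681/0.3306 = 20.6% | 0.195/0.545 = 0.36 |
| 50% | 0.0438/0.6563 = 6.7% | 0.0813/0.3438 = 23.6% | 0.15/0.65 = 0.23 |

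Over a wider range, OR runs from 0.84 (f = 10%, c = 40%) to 0.04 (f = 70%, c = 90%).

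**By timing of the item.** Simulation of a null item: 476 patients, m = 12.5%, c = 60%, 2,000 runs per cell, no unit effect. Death times are exponential with mean 5 or 10 days, truncated at 30, or uniform. Cells show the median OR and the share of runs in which the item looks protective at the 0.10 level (5% expected by chance).

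| Item due | Mean 5 days | Mean 10 days | Uniform |
|---|---|---|---|
| Day 0 | 1.00 (6%) | 1.00 (6%) | 1.00 (5%) |
| Day 1 | 0.65 (47%) | 0.78 (22%) | 0.91 (10%) |
| Day 2 | 0.45 (90%) | 0.64 (50%) | 0.84 (17%) |
| Day 9 | 0.07 (100%) | 0.20 (100%) | 0.48 (84%) |

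A random effect for unit would not remove this, because the bias arises within patients.

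**Arm effect.** Simulation with 238 per arm, true mortality 17% v 8%, and a null item given to 50% (control) v 90% (pathway) of those alive when it is due; mean death time 10 days, 400 runs, no clustering. The true arm OR is (0.08/0.92)/(0.17/0.83) = 0.42. With the arm alone, the estimate is about 0.42. With a day-2 item in the model it is 0.54; with a day-9 item, 1.05. The share of runs with p < 0.05 for arm falls from about 83% to 46% and 7%. These shares ignore clustering and are not the trial's power. A day-0 item leaves the arm OR nearly unchanged (0.41 without, 0.42 with).

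**Under a landmark.** Among patients alive when the window closes, counting later deaths only:

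OR = [m(1−f)c / ((1−m)c)] / [m(1−f)(1−c) / ((1−m)(1−c))] = 1.00.

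**The case against.** The strongest reply is that the article never says how a patient who dies before an item is due is scored. Study evaluations speaks of quality indicators at discharge, which could well be computed among discharged patients only. Early deaths would then drop out of those regressions and the odds ratios above would not arise. Denominators are also a detail that a condensed article may leave to the full protocol. This stands: counting deaths as not given is an inference, and the point must be conditional on it.

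The phrase about study variables could also mean only the case-mix variables under Study subjects; the sentences on selection and multicollinearity suit that reading. The Discussion calls organized care an outcome measure, and the outcomes in objectives 2 and 3 are not confined to 30-day death. All this is fair. But the sentence sets no such limit, both objectives ask for effects on outcomes, and no other model is described for them. That is a rule stated too broadly, rather than a detail left out.

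Three stronger readings are tempting and are not supported. A reader might infer that the indicator–mortality question cannot be answered at all; a landmark analysis answers part of it with the early indicators. A reader might infer that the trial will credit discharge planning with saving lives; no section says so. And a reader might infer that the primary result is invalid; the arm comparison is affected only if the indicators enter its model. Nor can one say that it is safe, because one procedure is described for arm and variables, and only age is named as forced in.

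**Conclusion.** The concern holds in conditional form. If the Table 2 and 3 indicators enter the 30-day mortality model as its wording allows, and deaths before an item is due count as not given, the direction of bias is certain and its size is not. It is large for the seven discharge-or-later items, smaller for the five with 24–48 hour windows, and about nil for same-day items. At 70% delivery a null item gives OR 0.55 or 0.23, as 20% or 50% of deaths precede it. The article gives neither death timing nor delivery rates, so these figures illustrate and do not predict. Possible absorption of the arm effect rests on the further assumption that delivery differs between arms.

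**What to change.** Replace the open-ended rule in Data analysis with the following:

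1. The arm model for 30-day mortality contains arm, forced in, and only the baseline covariates named under Study subjects.
2. Only indicators whose window closes by 48 hours after admission are related to mortality, among patients alive at 48 hours, counting deaths from then to day 30 after onset.
3. Discharge, whole-stay and follow-up indicators stay out of any model of 30-day death and are reported by arm among eligible patients, with eligibility stated.
4. The stroke-unit-stay indicator joins a 24-hour condition to a whole-stay condition, so it is not used in step 2 unless the 24-hour part is recorded separately.
5. The indicator–mortality analyses are labelled observational.

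The cost is mainly in wording. Early deaths leave these secondary analyses but stay in the arm comparison. Precision falls: 12.5% of 476 is about 60 deaths in all, and fewer after 48 hours. Indicators with no stated time, including the Organized Care Index, do not qualify under step 2 unless a time is fixed for them. Confounding by stroke severity remains, since a landmark removes only the survival artefact.

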**Figure 1 F1:**
[figure not shown]
Flow diagram of the progress of the units through the trial.

Nine units were excluded because they did not meet the inclusion criteria and five units withdrew after the project commenced following a decision by their management (three units withdrew after project pre-test and two units withdrew after project kick off). One unit could not provide reassurance that they would not implement a pathway if assigned to the control group and therefore they were not included in the study sample. The remaining units were randomized to either of the two arms. A simple randomization was carried out before the intervention and patient recruitment started, using a computer-generated sequence with allocation concealment. Fourteen units were selected and randomized. Blinding of patients and clinicians was not possible.

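### With 14 randomized units, the primary random-effects logistic test states no small-sample reference distribution; run as the usual large-sample test at the planned ICC, its two-sided type I error is about 6% to 8%, not 5%

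*Protocol article*

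**What the plan says.** The Randomization section of the protocol article states: "Fourteen units were selected and randomized". The Study sample section gives the planning values as "7 clusters per trial arm, cluster size of 24 patients, ICC of 0.018".

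For the primary outcome, the Data analysis section says that differences in 30-day mortality "will be evaluated using random-effects logistic regression, thus accounting for the clustering effect". The decision rule follows in the same section: "Statistical significance will be defined as a two-sided p-value < 0.05". That section also fixes the covariate rule (backward selection at 0.10 with age forced in) and the software. It does not say whether the arm effect will be tested by a Wald or a likelihood-ratio statistic, how the model will be estimated, or against which reference distribution the statistic will be judged. It neither states nor rules out a small-sample correction.

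**The concern.** Treatment is allocated to units, so the arm effect is a contrast between 7 units and 7 units. About 12 degrees of freedom support it, however many patients are enrolled. A random intercept puts between-unit variation into the model, but with 14 units that variance is estimated poorly. In simulation at the planned ICC it is estimated as zero in 27% to 38% of trials, and the fit then reduces to ordinary logistic regression that ignores clustering. A normal or chi-square reference makes no allowance for this uncertainty.

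The consequence falls on the one comparison that decides the trial's conclusion. A mortality difference would be declared too often when there is none, and the confidence interval would cover less often than claimed.

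**Working it through.** **Inputs.** From Study sample: 7 units per arm, ICC 0.018, stated unit size 24, 238 patients per arm, mortality range 8% to 17%, pathway target 8%. From Data analysis: random-effects logistic regression, two-sided 0.05. Taking 17% as the control rate is an assumption (the upper end of the stated range).

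**The plan's own figure first.** The plan says that "a sample size of 476 patients (238 in each group) was required for the study to have 80% power at the 5% significance level". With 17% versus 8%, mean 12.5%:

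n = [z_alpha × sqrt(2 × 0.125 × 0.875) + 0.842 × sqrt(0.17 × 0.83 + 0.08 × 0.92)]² / 0.09²

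- One-sided 5% (z = 1.645): [1.645 × 0.4677 + 0.842 × 0.4634]² / 0.0081 gives 166, and 166 × 1.43 = 237.4, so 238.
- Two-sided 5% (z = 1.960): 211, and 211 × 1.43 = 301.7, so 302.

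The stated 238 therefore comes from normal quantiles with no allowance for few units. That it matches only one-sided is a separate matter.

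**Unit size.** 238 / 7 = 34 patients per unit, whereas 7 × 24 = 168 per arm. Since 24 and 238 do not agree, both unit sizes were examined.

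**Analytic check.** If the standard error behaves as though estimated on 12 degrees of freedom, using the cut-off 1.96 gives P(|t| > 1.96) = 7.4%. On 10 degrees of freedom it is 7.8%.

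**Simulation under no effect.** The settings were 7 + 7 units, a maximum-likelihood random-intercept logistic model (25-point Gauss-Hermite quadrature), arm as the only covariate and 8000 trials per row. The Monte Carlo standard error is sqrt(0.06 × 0.94 / 8000), about 0.3 points. Entries are rejection rates in percent.

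| ICC | Mortality | Unit size | Wald z | Likelihood ratio | Wald against t, 12 df | Unit-level t-test |
|---|---|---|---|---|---|---|
| 0.018 | 12.5% | 34 | 7.4 | 6.5 | 4.7 | 5.0 |
| 0.018 | 17% | 34 | 7.2 | 6.3 | 4.7 | 4.9 |
| 0.018 | 17%, beta-binomial | 34 | 8.1 | 6.9 | 5.3 | 5.4 |
| 0.018 | 8% | 34 | 7.0 | 6.4 | 4.6 | 5.0 |
| 0.018 | 17% | 24 | 6.7 | 6.1 | 4.1 | 5.0 |
| 0.018 | 17% | mean 34, CV 0.6 | 7.8 | 6.5 | 4.9 | 4.8 |
| 0.05 | 17% | 34 | 9.1 | 7.6 | 6.3 | 5.0 |
| 0 | 17% | 34 | 4.0 | 3.8 | 2.3 | 4.6 |

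Other runs at ICC 0.018 widen the ranges slightly: Wald z down to 6.1%, likelihood ratio down to 5.5%, and t with 12 df down to 4.0%. Overall at the planned ICC, Wald z is about 6% to 8%, the likelihood ratio about 5.5% to 7%, and t with 12 df about 4% to 5%.

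**Confidence interval.** The 97.5% point of t with 12 df is 2.179, and 2.179 / 1.960 = 1.11. The matching interval on the log-odds scale is therefore about 11% wider than the normal-based one.

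**Power at 17% versus 8%, 34 per unit.** Wald z about 71% (70.7% in 2000 runs); t with 12 df about 63% to 64% (63.2% in the same runs).

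**The case against.** The strongest objection is that the correction is only unstated, not excluded. This is a condensed article, and degrees of freedom are often left to an analysis plan, which is not shown. A random intercept is also a fair way to describe allowing for clustering, and the article makes no claim about exact small-sample level.

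Much of this stands. A reader might infer that the trial will use no correction, or that its actual type I error is 7% to 8%. The document supports neither. Silence does not show which test will be used, and nothing in the text says what the named software would report. The 7% to 8% figure belongs to the Wald z-test near the planned ICC with about 34 patients per unit. It is lower with the likelihood ratio, with the stated 24 per unit, or with a smaller ICC. Nor do the simulations include the forced age term or the backward selection, so they do not give the error rate of the full planned analysis.

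What does not stand is that nothing follows for the plan. The article names the model and threshold for the deciding comparison and presents the model as dealing with clustering. With 14 units, the model alone does not hold 5% unless the reference distribution is also suitable. At the planned ICC, both large-sample tests exceeded 5% in every setting examined.

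**Conclusion.** The point holds in conditional form. If the primary model is run with its usual large-sample test and the ICC is near the planned 0.018, the two-sided type I error is about 6% to 8% rather than 5%. At no effect, that means about 92% to 94% coverage for a nominal 95% interval. The excess is roughly 0.5 to 3 points, depending on the test and the unit size.

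The result rests on 7 units per arm, 24 to 34 patients per unit, mortality between 8% and 17%, and no covariates. It moves with the ICC: for Wald z it disappears at ICC 0 (about 4%) and grows to about 9% at ICC 0.05. It is a cheap improvement to the deciding test. It does not show that the planned analysis is invalid.

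**What to change.** Add one sentence to the Data analysis section: the arm effect from the random-effects logistic model will be tested against a t distribution with 12 degrees of freedom (14 units minus 2), and the confidence interval will use the same distribution. A permutation test over the unit allocations is an alternative. It is a different procedure, so one of the two should be named in advance as primary.

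The t reference is not exact everywhere. In simulation it rejects 2.3% at ICC 0 and 6.3% at ICC 0.05. A t-test on unit-level mortality rates stayed between 4.6% and 5.4% throughout and would make a useful supporting analysis, though it is optional.

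The drafting cost is small, but the power cost is not negligible: about 7 to 8 points at 17% versus 8% with 34 per unit (about 63% to 64% instead of about 71%). Part of that higher figure comes from a test that rejects too often.
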